## Abstract

**Background:**

If adults practice several motor tasks together, random practice leads to better transfer and retention compared to blocked practice. Knowledge about this contextual interference (CI) effect could be valuable to improve neurorehabilitation of children. We present the protocol of a randomised controlled pilot study investigating the feasibility of blocked practice vs. random practice of robot-assisted upper limb reaching in children with brain lesions undergoing neurorehabilitation.

**Methods:**

Children with affected upper limb function due to congenital or acquired brain lesions undergoing neurorehabilitation will be recruited for a randomised controlled pilot study with a 3-week procedure. In the control week (1), two assessment blocks (robot-assisted reaching tasks, Melbourne assessment 2, subscale fluency), 2 days apart, take place. In the practice week (2), participants are randomly allocated to blocked practice or random practice and perform 480 reaching and backward movements in the horizontal and vertical plane using exergaming with an exoskeleton robot per day during three consecutive days. Assessments are performed before, directly after and 1 day after the practice sessions. In the follow-up week (3), participants perform the assessments 1 week after the final practice session. The primary outcome is the immediate transfer of the Melbourne Assessment 2, subscale fluency. Secondary outcomes are the immediate retention, 1-day and 1-week delayed transfer and retention and acquisition during the practice sessions. We will evaluate the feasibility of the inclusion criteria, the recruitment rate, the scheduling procedure, the randomisation procedure, the procedure for the participants, the handling of the robot, the handling of the amount of data, the choice of the outcome measures and the influence of other therapies. Furthermore, we will perform a power calculation using the data to estimate the sample size for the main trial.

**Discussion:**

The protocol of the pilot study is a first step towards a future main randomised controlled trial. This low risk pilot study might induce some benefits for the participants. However, we need to place its results into perspective, especially concerning the generalisability, as it remains questionable whether improving reaching constrained within a robotic device will ameliorate daily life reaching tasks.

**Trial registration:**

ClinicalTrials.gov Identifier: NCT02443857

## Background

The population of children undergoing neurorehabilitation is as heterogeneous as the causes for brain dysfunction. Differentiating between congenital and acquired brain lesions is common. Children with congenital brain lesions are diagnosed most frequently with cerebral palsy. The prevalence of cerebral palsy seems to decrease in Europe (from 1.90 to 1.77 per 1000 live births between 1980 and 2003); it is still the most common cause for severe motor impairments in children [1]. Acquired brain injuries in children are less common. In Norway, for example, the incidence for moderate traumatic brain injury amounts to 0.024 per 1000 children and for severe traumatic brain injury 0.025 per 1000 children [2]. For stroke, the worldwide incidence ranges between 0.013 and 0.13 per 1000 children [3]. Both, congenital and acquired brain lesions interfere with the normal development of the brain, which causes impairments in sensory-motor and cognitive functions and limitations in activities that may significantly impact quality of life [4]. Hence, these children should be referred to paediatric neurorehabilitation.

Nowadays, most neuro-rehabilitation programmes, including those for paediatric neurorehabilitation, are based on motor learning principles [5–7]. The general goal of motor learning is to attain relatively permanent changes in movement skills by practice and experience [8]. It has been suggested that the performance during practice (i.e. acquisition), retention (i.e. the preservation of the learned skill for a certain period) and transfer (i.e. when transferring the learned skill to another task) needs to be distinguished [9]. While retention is sustainability of performance after a practice phase, transfer reflects the effect of the practice on other, yet untrained, tasks [9]. Transfer is especially important since it allows generalising improved motor functions or capacities to daily life performance.

If several tasks have to be learned and are practiced within the same therapy session, they can interfere with each other, which could affect the outcome. In this so-called contextual interference effect [10], the practice order is an important factor that determines the strength of this effect. If one task is practiced several times before switching to the next task (i.e. practicing in a blocked order), contextual interference is low [10]. If different tasks are practiced in a random order, interference is high [10]. Contextual interference has mainly been investigated in healthy adults where it was shown that high contextual interference leads to worse performance in acquisition but better performance in retention and transfer, while low contextual interference leads to contrary results [11, 12]. Two main hypotheses explaining these findings have been discussed in the literature. On the one hand, the elaborative-processing hypothesis states that compared to blocked practice, the learning process during random practice is based on a more-profound elaboration of the tasks due to the comparisons between and within the trials [13]. This could lead to a more comprehensive memory trace, which is easier to retrieve [14]. The forgetting-reconstruction hypothesis, on the other hand, is based on a strengthened memory consolidation occurring during random practice [15]. The underlying explanation is that during random order practice, the learner switches between different tasks all the time and forgets the established action plan of the prior task when a subsequent new task is performed [14]. It seems comprehensible that (a) a deeper elaborated and more robust memory representation could result in better retention and transfer and (b) acquiring a motor skill under blocked practice might be easier because of less disturbance, leading to a better momentary performance at acquisition compared to random practice.

It has been stated that the contextual interference effect is larger when the tasks involve different motor programmes [11, 16]. A motor programme can be understood as a memory for a movement class rather than for an action or a movement solely [17, 18]. Actions that have the same invariant aspects in common (e.g. spatial and topographical characteristics of the action [19], relative force and timing and sequences involved in the action [11]) are controlled by the same motor programme [11, 16]. Therefore, applying variations of the invariant features would increase the contextual interference effect. However, as contextual interference has mainly been investigated in healthy adults, evidence is lacking for children with congenital or acquired brain lesions [20].

Adhering to the recommendation of providing intensive and repetitive training to restore motor function in neurorehabilitation [21] is challenging, especially when working with children. To keep them engaged during highly repetitive therapy sessions, practice has to be variable. To induce variability, several tasks or variations of a task are practiced usually within one therapy session. Since we aim to provide efficient therapies to obtain optimal outcomes, we consider it relevant to improve our understanding of the influence of contextual interference on the therapeutic outcome of paediatric neurorehabilitative interventions.

In recent years, rehabilitation technologies have been applied increasingly also in paediatric neurorehabilitation [22]. Main advantages are the standardisation of training protocols and assessments, high number of repetitions, and above all, additional motivation due to exergames [22]. While the definition of ‘exergame’ is debated, in this study, we use the common definition ‘videogames that require physical activity in order to play’ p. 10 [23]. To our knowledge, two studies used new technologies to investigate the influence of the practice order. The first study investigated motor learning in children with developmental coordination disorder and typically developing children. The children practiced with the Nintendo® Wii Fit video game during 10 20-min sessions in a variable group (a self-selected choice out of 10 games) and a repetitive group (the same game throughout the whole session) [24]. In the second study, children with cerebral palsy and typically developing children practiced a computer-maze in random order (30 trials, 5 different mazes in random order) and in constant order (30 trials of 1 maze) [25]. While both practice groups improved their game performance similarly in the first study [24], the random order group showed a reduction in movement time needed to complete the maze tasks in retention and transfer in the second study [25]. However, as both studies did not include a true blocked group, we designed a study protocol to investigate blocked vs. random order. As there is not much knowledge in the field of contextual interference with robotic exergames in paediatric neurorehabilitation, we planned a pilot study to evaluate the feasibility of a future main study. The objective of this paper was to present *the protocol* of this pilot study evaluating the feasibility of a randomised controlled, single-blinded study about contextual interference in robot-assisted upper limb training in children with congenital or acquired brain lesion and affected upper limb function. To assess the feasibility, we aimed to address the following questions:
Are the chosen inclusion criteria specific enough to result in a sample of participants, which is suitable for this pilot study?Is the recruitment rate feasible?Is the scheduling procedure feasible?Is the randomisation procedure feasible?Is the whole procedure feasible for the participants?Is the handling of the robot feasible?Is the handling of the large amount of data feasible?Are the outcome measures responsive and sensitive enough within this setting?Is there a confounding influence of parallel therapies within the rehabilitation setting?Is it feasible to conduct the main trial with respect to the needed sample size calculated from the data obtained for the primary motor learning outcome?

## Methods

### Design

This pilot study protocol describes a randomised controlled single-blinded two-arm intervention study comparing several outcome time points between two groups of children with neuro-motor upper limb impairment who will practice two variations of reaching movement tasks with robot-assisted exergames (one group in blocked, the other in random order) with a predefined primary outcome and a follow-up period of 1 week. We will include a follow-up period of 1 week to match the rather short intervention period; 1 week will also be feasible to plan within a rehabilitation stay.

### Setting

The study will take place at the Swiss Children’s Rehab of the University Children’s Hospital Zurich in Affoltern am Albis, Switzerland. All measurements and practice sessions will be performed during a multidisciplinary in-patient rehabilitation stay.

### Ethical considerations and reporting

This study has been approved as part of the ChARMin project (sub-project 5: Motor learning) by the Ethics Committee of the Canton Zurich (BASEC-Nr. PB_2016-02450) and the Swiss Agency for Therapeutic Products (Swissmedic reference number: 2015-MD-0009).

According to the Ethics Committee’s guidelines, all the participants will give their verbal consent, children of 15 years and older and all the legal representatives will provide informed written consent.

This study protocol was established according to the guide on reporting protocols of pilot and feasibility trials [26], the Consolidated Standards of Reporting Trials (CONSORT) statement extension for randomised pilot and feasibility trials [27] and the Standard Protocol Items: Recommendations for Interventional Trials (SPIRIT) [28]. See Additional file 1 for the SPIRIT checklist and Fig. 1 for the SPIRIT Figure.

**Fig. 1 Fig1:**
[figure not shown]
Standard Protocol Items Recommendation for Interventional Trials (SPIRIT) figure. Actions and appointments throughout the whole study. *The test of nonverbal intelligence is conducted before the first practice session (outcome needed for randomisation by minimisation). **Allocation is done when all the parameters for minimisation are obtained; at latest on the day before the first practice session

### Participants

The majority of children admitted to our rehabilitation centre has a congenital brain lesion (cerebral palsy) but we treat also children with acquired brain lesions (after stroke or traumatic brain injury), spinal cord injury, genetic syndromes, etc. The reasons for admitting a patient vary. Most children with cerebral palsy come to the centre for a shorter period (4 to 6 weeks) of intensive therapy or after orthopaedic surgery, particularly of the lower limbs, with consecutive rehabilitation. Patients who experienced an acquired brain lesion, such as a stroke or traumatic injury, are admitted as soon as they are stable and can leave the intensive care unit. Depending on the recovery, some of these patients might also be re-admitted for rehabilitation at a later stage. Currently, the average length of stay is around 40 days but varies from a couple of weeks to more than a year (for children with acquired brain lesions). According to their rehabilitation goals, the children undergo physiotherapy, occupational therapy, sports therapy, speech and language therapy, neuropsychology, hippotherapy, and robot-assisted therapy. For this pilot study, we will recruit a sample representing patients with congenital or acquired brain lesions, reflecting the majority of our inpatient population.

#### Inclusion and exclusion criteria

Included will be children with either congenital or acquired brain lesions. Those with an acquired brain lesion should be in the subacute, i.e. more than 3 months, or chronic stage. Further inclusion criteria will be uni- or bilaterally affected upper limb function with spasticity, dyskinesia or mixed conditions. Additional inclusion criteria will be age 5 to 18 years, the ability to sit upright for approximately 60 min without lateral trunk support and a Manual Ability Classification System (MACS) level between I and IV (MACS level I: handles objects easily and successfully; level II: handles most objects but with somewhat reduced quality and/or speed of achievement; level III: handles objects with difficulty, needs help to prepare and/or modify activities; level IV: handles a limited selection of easily managed objects in adapted situations [29]).

Moreover, the children will need to be able to understand and follow test instructions, be compliant for the whole study procedure, can communicate pain or discomfort and see a computer screen at approximately 1 m in front of him/her. Excluded will be children with upper limb surgery or Botox injections during the past 6 months, and upper limb skin lesions.

We decided not to include outpatients since we learned from prior experiences that it is difficult for parents to organise their children’s attendance for participating in such an extensive study procedure.

### Target sample size

Since the recruitment rate will be one of our feasibility criteria, we will recruit for 1 year and calculate the recruitment rate, taking into account the number of eligible and recruited participants, and complete datasets. Yet, the CONSORT 2010 statement extension to randomised pilot and feasibility trials recommends to give some rationale for the target sample size [27]. Based on our center’s numbers from past years and taking into account the inclusion criteria, we anticipate to recruit 20 participants (10 per group).

### Recruitment

We will inform the children who are admitted to our centre matching the inclusion criteria and their parents/legal representatives about the study. If they provide their written informed consent, the children will be included and the appointments scheduled.

### Group allocation

Participants will be allocated to a blocked or random practice group using randomisation by minimisation. This method enables balancing several prognostic factors in small samples [30]. We will impute parameters that potentially influence motor learning. To reduce the risk of selection bias, these factors should be balanced between the groups, even in the case of uneven distribution.

We will use the following minimisation parameters: age (preschool age: 5–6 years, primary school age: 7–12 years, secondary school age and older: 13–18 years); gender (female, male); diagnose (congenital, acquired); manual ability (MACS level I, II, III or IV); and cognitive ability according to the Test of Nonverbal Intelligence–Fourth edition (TONI-4), which evaluates abstract reasoning and problem solving (Index Score < 70: very poor, 70–79: poor, 80–89: below average, 90–110: average, 111–120: above average, 121–130: superior and > 130: very superior) [31]. The minimisation parameters are equally weighted. A study nurse will receive the minimisation parameters of each new participant by one of two researchers involved in recruitment. She will enter the parameters in a custom-written Matlab programme, which will allocate the participant to either the blocked or random order group. The study nurse will be unaware of this definition and the purpose of the study. The study nurse will enter the allocation in a file, which will allow the researcher to schedule the appointments and perform the practice and measurement sessions. The study nurse will not be involved otherwise in this trial. In case the study nurse is unavailable, we will assign another independent person who will perform this procedure.

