#### Analysis of motor learning outcomes of the main trial

As recommended by the CONSORT extension to pilot and feasibility studies, we will report 95% confidence interval estimates of the motor learning outcomes [27], as the study will be most likely underpowered. Hypothesis testing will only be conducted if the recruited sample size is large enough to warrant sufficient statistical power.

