##### Primary outcome

***Immediate transfer*** The relative difference $$ \left(\frac{MA{2}_4- MA{2}_3}{MA{2}_3}\right) $$ of the MA2_fluency_ sum score between the time point right before the first practice session (MA2_3_) and the time point immediately after the last practice session (MA2_4_) will be compared between the groups. A *T* test (or Mann-Whitney *U* test, if data are not normally distributed) will be performed.

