##### Secondary outcomes

For all secondary outcomes, a multifactorial repeated measures analysis of variance (ANOVA) with ‘practice group’ and ‘time point’ as factors will be conducted over all the time points. A post-hoc analysis (Bonferroni correction for multiple comparisons) will be used to test for significant changes between the appropriate time points.

***Delayed transfers*** The MA2_fluency_ sum scores will be compared between the time point right before the first practice session, 1 day after the last session (1-day-delayed transfer), and 1 week after the last session (1-week-delayed transfer).

***Immediate retention, delayed retentions, acquisition*** For the several retention time points and the acquisition, the parameter nP_norm_ (obtained during the exergame tests and the practice sessions, respectively) will be evaluated. Comparisons will be made between the data obtained during the exergame tests right before the first practice session with the data from immediately after the last practice session (immediate retention), 1 day after the last practice session (1-day retention), and 1 week after the last practice session (1-week retention). For the acquisition, all the data points obtained during the practice trials will be compared.

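### Allocation is minimised on five factors expected to influence motor learning, but no stated analysis uses them; if they are prognostic, the unadjusted intervals and the main-trial sample size are conservative

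*Protocol article*

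**What the plan says.** Protocol article, Group allocation: "Participants will be allocated to a blocked or random practice group using randomisation by minimisation". The reason given for choosing the factors is "We will impute parameters that potentially influence motor learning", and the method is preferred because "This method enables balancing several prognostic factors in small samples". The factors carry equal weight. They include "age (preschool age: 5–6 years, primary school age: 7–12 years, secondary school age and older: 13–18 years") and "gender (female, male); diagnose (congenital, acquired); manual ability (MACS level I, II, III or IV"), plus seven TONI-4 bands.

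The analysis sections then fix the following:

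- Main output: "we will report 95% confidence interval estimates of the motor learning outcomes", because the study is expected to be underpowered (Analysis of motor learning outcomes of the main trial).
- Primary outcome: the relative change in MA2 fluency is compared between groups. "A *T* test (or Mann-Whitney *U* test, if data are not normally distributed) will be performed". No covariate is named.
- Secondary outcomes: a repeated measures ANOVA with practice group and time point "as factors will be conducted over all the time points". No other factor is named.
- Question 10 (Analysis of feasibility): the main-trial n uses the pooled, unadjusted SD of the pre-post differences.

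**The concern.** When allocation forces balance on variables that predict the outcome, the difference between arm means varies less from trial to trial than under simple randomisation. The two-sample standard error does not know this. It still counts the between-child variance due to those variables, so the interval is wider than the design requires.

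Two outputs are affected. The first is the 95% interval for the group difference, which is the pilot's chosen way of reporting motor learning. The second is the SD for question 10, which helps decide whether a main trial is feasible at a centre that expects about 20 recruits a year. Because the article itself names the tests, the model factors and the SD, this is a mismatch within the stated plan and not a detail left to another document.

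**Working it through.** **Inputs from the protocol.** N = 20 (10 per group); five equally weighted factors with 3, 2, 2, 4 and 7 levels; two-sided alpha 0.05 (z = 1.96); power 80% (z = 0.84). N = 20 rests on expected recruitment, so there is no power figure to reproduce.

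**Assumptions.** The case mix; the share of variance in change explained by the factors (R2); and the probability of assigning to the arm favoured by minimisation (1.0 or 0.8). The protocol gives none of these. Total SD is set to 1 and the true difference to 0.

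**Check 1: is the unadjusted interval miscalibrated?** 3,000 simulated trials per setting, linear factor effects. Widths are full widths in SD units, with assignment probability 1.0.

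| R2 | Unadjusted coverage (prob. 1.0 / 0.8) | Unadjusted width | Five scores, 5 df | All levels, up to 13 df (mean) |
|---|---|---|---|---|
| 0 | 95.3% / 95.1% | 1.86 | 2.03 | 2.84 |
| 0.1 | 95.6% / 95.2% | 1.86 | 1.92 | 2.67 |
| 0.2 | 96.4% / 95.9% | 1.85 | 1.81 | 2.51 |
| 0.3 | 96.7% / 96.6% | 1.86 | 1.70 | 2.35 |
| 0.5 | 97.9% / 97.2% | 1.87 | 1.44 | 2.01 |

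Under simple randomisation the same t interval covers 94.4% at both R2 = 0.3 and R2 = 0.5, so the excess comes from analysing a minimised design as if it were not minimised. The five-score model keeps 94.7-95.3% coverage.

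**Check 2: how many covariates can n = 20 carry?** Indicators for all levels need 2 + 1 + 1 + 3 + 6 = 13 df out of 20 - 2 = 18. That interval is still wider than the unadjusted one at R2 = 0.5 (2.01 against 1.87).

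**Check 3: what do two scores (MACS level, age) gain?** Half-widths in SD units, over both assignment probabilities.

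- The two carry most of the effect: R2 = 0.3, from 0.94 to 0.85-0.86 (9-10% narrower); R2 = 0.5, from 0.93 to 0.76-0.78 (16-18% narrower).
- All five matter equally: R2 = 0.3, from 0.93 to 0.90-0.91 (2-4% narrower); R2 = 0.5, from 0.93 to 0.86-0.88 (about 6-8% narrower), with coverage still 96.4-97.2%. At R2 = 0.2 there is at most a 1% gain; at 0.1 the interval is 1-2% wider.
- No factor matters: 3-5% wider.

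**Check 4: sample size.** The formula in question 10 is n = (1.96 + 0.84)^2 x 2 x sigma^2 / delta^2 = 15.68 x sigma^2 / delta^2, read as n per group. For an assumed difference of half an SD, n = 15.68 / 0.25 = 62.7, so 63. If the covariates in the main-trial model explain a share R2 of the variance, sigma^2 becomes (1 - R2) x sigma^2. At R2 = 0.3, n = 62.7 x 0.7 = 43.9, so 44. At R2 = 0, n does not change.

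**The case against.** The strongest reply is that everything depends on an R2 the protocol does not give. It says only that the factors may influence learning, and they may predict a child's level of fluency far better than its relative change. At R2 of 0.1 or less, coverage is close to nominal and even a lean adjustment widens the interval slightly. This stands, and it is why the point is conditional.

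A second reply is that MACS and age are not ranked above the other factors, so a two-score model may capture only part of the effect. This also stands: with equal effects the gain is small and some over-coverage remains.

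Third, in a group-by-time ANOVA stable differences in level between children leave the within-subject error, so the factors matter there only through their relation with change over time. That is right, and the point is therefore limited to the between-group comparison of change.

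Finally, the error is conservative, the pilot is about feasibility, and omitting covariates at n = 20 can be defended. That lowers the urgency. It does not explain why factors judged important enough to steer allocation appear in no stated analysis, or why the sample size for a larger trial, where the df cost is small, should rest only on the unadjusted SD.

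**Conclusion.** The mismatch between allocation and analysis is real. If the minimisation factors predict the change in MA2 fluency, the unadjusted 95% interval covers about 96.5-97% at R2 = 0.3 and 97-98% at R2 = 0.5, and the main-trial n from the unadjusted SD exceeds what an adjusted analysis needs. These figures rest on n = 20, an assumed case mix and an assumed R2.

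A reader might infer that the planned intervals will certainly be too wide, or that adding MACS and age will certainly correct them. The document supports neither: it gives no strength of association, and the gain at n = 20 runs from none (R2 of about 0.2 or less with equal factor effects) to about 20% (R2 = 0.5, mostly through MACS and age). Nor is there any bias or inflated type I error. It is a question of precision and calibration, worth settling before the data are seen.

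**What to change.** 1. For the between-group comparison of change, pre-specify a linear model with practice group and a small set of minimisation factors entered as scores, for example MACS level and age in years. Report its 95% interval beside the unadjusted one. Do not adjust for all factor levels at n = 20.
2. State that the main trial's primary model will adjust for all five minimisation factors.
3. For question 10, report n from the unadjusted SD and from the residual SD of the parsimonious pilot model. Say that the second applies only if the main-trial analysis is adjusted.

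The cost is wording plus a move from a T test to a linear model for the added estimate; the minimisation variables are already collected in week 1. Statistically it costs two degrees of freedom and an interval about 3-5% wider if the factors prove not to be prognostic. Keeping the unadjusted interval alongside lets readers see that.
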